## Background

The incidence of oropharyngeal squamous cell carcinoma (OPSCC) is rapidly increasing, associated with rising rates of oral infection with the human papillomavirus (HPV) [1]. Patients with HPV-related cancers tend to present at a younger age and experience markedly improved survival, compared to patients with smoking- and alcohol-related head and neck cancers [1]. In such young patients with good prognosis, survivorship is of paramount importance, as they are likely to survive their cancer and may have to cope with the side effects of therapy and secondary disability for decades. Optimizing post-treatment quality of life (QOL) for patients with OPSCC has become one of the most important issues in head and neck oncology.

Historically, oropharyngeal cancer was frequently managed with open surgery, with or without postoperative radiotherapy (RT). Although this approach was reasonably effective at obtaining tumor control, the speech, swallowing and cosmetic outcomes were poor. Surgical access of the oropharynx traditionally involves large facial and neck incisions that interrupted critical neurovascular and muscular structures [2]. This resulted in high complication rates, leading many centers to move towards organ preservation approaches utilizing radiation as primary treatment with surgery reserved for salvage [3]. Although a randomized trial was never carried out comparing surgery and RT, a meta-analysis of observational studies demonstrated that primary surgery and primary RT approaches were equivalent in terms of survival, but major complications of therapy were markedly worse in the primary surgery patients [2].

For patients with high-risk cancers of the oropharynx, concurrent cisplatin-based chemotherapy is delivered with RT and achieves a significant improvement in survival, compared to radiotherapy alone [4]. However, it is increasingly recognized that these improvements in survival come at the cost of increased acute and late toxicities: these include dysphagia, mucositis, xerostomia, fibrosis, osteoradionecrosis, neutropenia, neurotoxicity, nephrotoxicity and ototoxicity [5]. The addition of chemotherapy to RT increases the risk of long-term gastrostomy tube dependence from 1% to 13% [5]. These treatment-related toxicities can significantly affect QOL.

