### Measurement of response

Survival outcomes: Overall survival will be measured as time from randomization until death from any cause, and progression-free survival as time to either progression or death, whichever occurs first.

QOL outcomes: The MDADI, EORTC scales, NDII, and VHI-10 will be measured at baseline and at 6-month intervals. PNQ will be completed at 1 year post-treatment.

Toxicity outcomes: CTC-AE toxicities will be recorded at every follow-up visit (3, 6, 9, 12, 15, 18, 21, 24, 30, 36, 42, 48, 54, and 60 months from the first date of treatment).

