### Statistics and sample size calculation

The study will employ a 1:1 randomization between Arm 1:Arm 2 (Figure 1) in a permutated block design. This sample size allows for one stratification factor at randomization, which will be HPV status: (positive vs. negative/indeterminate)

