### Sample size considerations

This study will employ a randomized phase II screening design, to conduct a definitive QOL comparison as the primary endpoint, along with preliminary and non-definitive overall survival comparison between the two arms as a secondary endpoint [17]. The primary endpoint is the total score on all twenty items of the MDADI. It is generally believed that a 10-point difference in standardized QOL scores represents a clinically significant difference in QOL [18]. It is assumed that the QOL scores will be normally distributed with a standard deviation of 12. The study will use a two-sided, independent-sample t-test with an alpha level of 0.05 and power of 90%, and assume a dropout rate of 10%. There will be a 1:1 randomization between Arm 1 and Arm 2. In order to detect a 10-point improvement in QOL in the TORS arm (Arm 2), a total of 68 patients will be required (34 in each arm). Accrual targets are as follows: 10 patients in year 1, and 15–20 patients in years 2, 3, and 4.

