### Analysis plan

Patients will be analyzed in the groups to which they are assigned (intention-to-treat).

An independent-sample t-test will be used to compare QOL scores at 1-year on the MDADI. The percent of patients in each arm who experience a clinically significant QOL decline (10 points) will also be reported. Survival will be calculated from date of randomization using the Kaplan-Meier method with differences compared using the log-rank test. Pre-planned subgroup analysis will occur based on the stratification variable. A Cox multivariable regression analysis will be used to determine baseline factors predictive of survival. For the secondary endpoints involving QOL scales, linear mixed effects models will be used; for the MDADI, NDII and VHI-10, the total scores will be compared between the two arms, whereas for the EORTC scales, each of the subscales (e.g. pain, swallowing, etc.) will be compared between the two arms. The PNQ scores (A to E) will be converted to a numerical score (0 to 4, respectively), and the mean scores in each group will be compared with a t-test. In addition, the proportion of patients reporting severe neurological dysfunction (D or E) will be compared with the Chi-Squared Test, or Fisher's exact test, as appropriate.

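### HPV status stratifies the randomization but, as written, not the survival comparison: a modest, avoidable loss of efficiency, alongside a Cox model that promises more than the expected deaths can support

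*Protocol article*

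**What the plan says.** Four statements in the protocol article bear on this.

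- Statistics and sample size calculation: "This sample size allows for one stratification factor at randomization, which will be HPV status", with two levels, positive and negative/indeterminate.
- Background: patients with HPV-related cancers "experience markedly improved survival, compared to patients with smoking- and alcohol-related head and neck cancers".
- Analysis plan, on the comparison of arms: "Survival will be calculated from date of randomization using the Kaplan-Meier method with differences compared using the log-rank test". The stratification factor is mentioned once in that section: "Pre-planned subgroup analysis will occur based on the stratification variable". Measurement of response lists OS and PFS together as the survival outcomes, so the sentence is naturally read as covering both. The interim OS stopping rule in the Data Safety Monitoring Committee section also names the log-rank test without qualification.
- Analysis plan, on prognostic factors: "A Cox multivariable regression analysis will be used to determine baseline factors predictive of survival". No covariates, limit on their number or expected death count is given.

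Sample size considerations limits the weight of the survival results: the trial makes its QOL comparison "along with preliminary and non-definitive overall survival comparison between the two arms as a secondary endpoint".

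**The concern.** Stratified permuted blocks balance the arms within each HPV level, which removes most of the chance imbalance in a strong predictor of death. An unstratified log-rank test computes its variance as if that imbalance could still occur. The variance is then too large, the test rejects too seldom under the null, and some power is lost. A hazard ratio that omits a strong prognostic factor is also pulled toward 1 relative to the within-stratum effect.

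The Cox model raises a separate issue. Its stated purpose is to *determine* baseline predictors, but a 68-patient trial in T1-2 disease will see few deaths. Prognostic factors picked from an open list on so few events would be unstable.

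What is at stake is limited: how well the trial uses its few deaths when it informs the design of the phase III survival trial. The MDADI primary endpoint is not affected.

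**Working it through.** **The plan's own figure.** The article gives no event count, hazard ratio or power for survival. Its only sample size figure is for the MDADI: 2 × (1.960 + 1.282)² × 12² / 10² = 30.3 per arm. Dividing by 0.9 for dropout gives 33.6, hence 34 per arm and 68 in total. This reproduces the plan. The survival analyses take whatever deaths those 68 patients supply.

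**Expected events.** The inputs are the outcome rates quoted in the Background, extrapolated with exponential survival (an assumption). Visits run to 60 months. Events at 5 years = 68 × (1 − S^(5/t)), where S is survival at t years.

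| Source rate | Events at 5 years |
|---|---|
| TORS, 2-year OS 90% | 68 × (1 − 0.90^2.5) = 15.7 |
| TORS, 2-year OS 82% | 68 × (1 − 0.82^2.5) = 26.6 |
| CRT, 3-year OS 85% | 68 × (1 − 0.85^(5/3)) = 16.1 |
| CRT, 3-year OS 51% | 68 × (1 − 0.51^(5/3)) = 45.9 |
| PFS, from TORS 2-year DFS 89% to 79% | 68 × (1 − 0.89^2.5) = 17.2 to 68 × (1 − 0.79^2.5) = 30.3 |

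The 51% figure comes from CRT series with 31-86% T3/T4 tumours, so it is an upper extreme for a T1-2 trial. If the analysis is run one year after accrual ends (10 patients in year 1, then about 19 a year, mid-year entry), the TORS rates give about 9-16 deaths.

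**Power of the survival comparison.** By Schoenfeld's formula, power = Φ(|ln HR| × √d / 2 − 1.96). For HR 0.5:

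- 16 deaths: Φ(0.693 × 4.00 / 2 − 1.96) = 28%
- 27 deaths: Φ(0.693 × 5.20 / 2 − 1.96) = 44%
- 80% power needs 4 × (1.960 + 0.842)² / 0.693² ≈ 66 deaths

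**Stratified against unstratified log-rank.** These are simulated trials of 68 patients with allocation stratified by HPV and five years of follow-up. HPV prevalence and prognostic effect are assumed, because the article gives neither.

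| Assumed setting | Type I error, unstratified | Type I error, stratified | Power, unstratified to stratified |
|---|---|---|---|
| 60-75% HPV-positive, HPV hazard ratio 3-5 (6,000 trials per setting) | 3.0-4.0% | 5.0-5.1% | HR 0.4: 31-36% to 39% |
| 85% HPV-positive; 3-year OS 90% v 60% (5,000 trials) | 3.8% | 5.4% | HR 0.5: 17% to 20% |
| 70% HPV-positive; 3-year OS 90% v 60% (5,000 trials) | 3.0% | 4.6% | HR 0.5: 22% to 27% |
| 60-85% HPV-positive, HPV hazard ratio 3-5 | 2.7-4.3% | 4.7-5.5% | gain of 2-7 points |

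The 90% v 60% survival split corresponds to an HPV hazard ratio of ln 0.60 / ln 0.90 = 4.8. With 5,000 trials the simulation standard error at 5% is √(0.05 × 0.95 / 5000) = 0.3 points, so stratified values of 4.6% and 5.4% are compatible with 5%. Across all settings the power difference is about 2-8 points. The attenuation of the hazard ratio was not quantified.

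**Size of the smaller stratum.** In the 85% and 70% HPV-positive settings under the null, the HPV-negative stratum held on average 5.8 of 15.2 deaths and 11.7 of 19.4 deaths.

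**Cox model capacity.** Ten events per parameter is a rule of thumb, and five is a lenient version.

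- 16-27 deaths: 1.6-2.7 parameters at ten per parameter, or 3.2-5.4 at five
- 46 deaths (upper extreme): 4.6 parameters at ten per parameter

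Arm and HPV status already use two.

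**The case against.** The strongest reply is that the text never says the test is unstratified. It is silent, this is a condensed article, and stratification of a log-rank test and the covariates of a Cox model are often fixed in a full protocol or SAP. That stands as far as it goes. If either document already specifies a stratified test, the log-rank half of this point falls away. But the Analysis plan does say how the stratification factor will be used, and names only subgroups. The ordinary reading of the sentence is therefore the plain test.

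It is also fair that little turns on the choice. The plain test does not inflate false positives, neither version is usefully powered, and the protocol declares the comparison non-definitive.

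A reader might infer three stronger things that the document does not support:

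- *That wrong hazard ratios will be carried into phase III.* A log-rank test yields a p-value, the Cox model is assigned to prognostic factors, and nothing says that a hazard ratio from either will size the next trial. Attenuated and imprecise is as far as one can go.
- *That the Cox model is overfitted.* No covariate list is fixed, so this would be presumed. HPV status is a required baseline item and could be included.
- *That only 10-18 deaths will be available.* That is the 3-year count from the TORS rates (68 × (1 − S^1.5) = 9.9 to 17.5). Follow-up is planned to 60 months, and the CRT rates would add more.

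**Conclusion.** The point holds as a modest, free improvement. HPV status is the only randomization stratum and is strongly prognostic on the protocol's own account, so the survival comparison should use it. Taken as the ordinary log-rank test, the stated method is valid but conservative: about 3-4% type I error in place of 5%, about 2-8 points of power lost, and an effect estimate drawn somewhat toward 1. These sizes depend on the assumed HPV prevalence (60-85% positive) and HPV hazard ratio (about 3-5). The direction follows from stratified allocation on a prognostic factor. No conclusion is biased, and the primary endpoint and the sample size of 68 are untouched.

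The secondary point holds regardless of how the log-rank test is specified. With about 16-27 deaths at five years under the TORS rates, or up to about 46 at the extreme of the CRT range, a multivariable Cox model can describe a few terms but cannot settle which baseline factors are prognostic. The non-definitive label is attached to the comparison of arms and is not repeated for this model.

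**What to change.** - In the Analysis plan, specify the log-rank test stratified by HPV status for OS and PFS, and report a treatment hazard ratio with its confidence interval from a Cox model stratified by HPV. Use the stratum recorded at randomization (p16-based), not the later PCR result.
- Use the same stratified test in the interim OS rule, for consistency. It will change little in practice: one year of follow-up on 30 patients gives about 30 × (1 − 0.90^0.5) = 1.5 to 30 × (1 − 0.82^0.5) = 2.8 deaths at the TORS rates.
- State that the HPV-negative/indeterminate stratum may be sparse and may contribute little to the stratified test.
- Limit the multivariable Cox model to a few pre-named terms, such as arm and HPV status, and call it exploratory. A penalized fit or a further covariate once deaths allow is a matter of preference.

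The cost is a few sentences, with no extra patients, visits or data. The price is that fewer baseline factors are explored.

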### Data Safety Monitoring Committee (DSMC)

The DSMC, consisting of at least one radiation oncologist, one medical oncologist, and surgical oncologist not involved in the study, will meet quarterly after study initiation to review toxicity outcomes. If any grade 3–5 toxicity is reported, the DSMC will review the case notes to determine if such toxicity is related to treatment. If the DSMC deems that toxicity rates are excessive (e.g. >5% grade 4 or 5 toxicity), then the DSMC can, at its discretion, recommend modification or cessation of the trial.

*Interim analysis*: the DSMC will conduct one interim analysis once 30 patients have been accrued and followed for 1-year. For this analysis, the DSMC will be blinded to the identity of each treatment arm, but QOL and OS data will be presented for each arm.

The DSMC will recommend stopping the trial if there is an OS difference that is statistically significant with a threshold of p < 0.001 using the log-rank test, based on the Haybittle-Peto stopping rule; this retains an overall alpha of 0.05. Furthermore, if the QOL scores among all patients are substantially different than estimated in the sample size calculation, the DSMC can recommend increasing or decreasing the target accrual in order to maintain statistical power.

### Biomarker studies

#### Human papillomavirus testing

P16 testing (which is an excellent surrogate marker of HPV status) is required for stratification at the time of randomization. This will be done through the routine pathology laboratories as per current routine clinical care.

The accompanying biomarker study will determine HPV status by real-time polymerase chain reaction (PCR), not for the purposes of randomization, but to confirm the accuracy of P16 results and also for subtyping of HPV strain. For patients randomized to radiotherapy, pre-treatment formalin fixed paraffin embedded (FFPE) primary site biopsy specimens will be retrieved in 10 slides 8um thick from the FFPE blocks. For patients randomized to TORS, the main specimen will be taken to pathology frozen section room and a portion from the center of the specimen will be taken with the assistance of the pathologist and frozen at -80 degrees Celsius. DNA will be extracted from the specimens for HPV testing by real-time PCR.

### Mutational and copy number variation analysis

DNA will be extracted either from formalin fixed specimens or preferably fresh tumor for patients undergoing TORS as well as 10 mL of venous blood drawn prior to the initiation of treatment. Specimens yielding DNA of adequate quantity and quality (>5 μg, OD between 1.8 and 2.0) will be subjected to high-throughput sequencing and gene copy number analysis.

## Discussion

In the wake of the HPV oropharyngeal cancer epidemic, it is imperative that we have treatment strategies that optimize post-treatment QOL for these younger, healthier patients. Radiation therapy (+/- chemotherapy) has been proven highly effective and provides a high QOL for most patients; however, a subset can suffer significant toxicity including severe dysphagia requiring gastrostomy tube dependence. Although the preliminary outcomes of TORS are encouraging, rapid adoption has occurred in the United States without clear evidence that it provides equivalent or superior QOL and survival outcomes. It is critical that this question be answered in a systematic way to either support this change in treatment strategy or halt this transition. The results of this study have the potential to guide improvements in the QOL of patients with OPSCC in Canada and worldwide.

The implementation of new technologies in medicine often follows Roger’s innovation adoption life-cycle: after the technique is developed by innovators, it is taken up by early adopters, followed by the early- and late- majority, and then laggards in a bell-curve distribution [19]. The ideal time to test a new innovation is at the early-adoption/early majority phase, as after a technique is widely adopted, benefits can be assumed (sometimes erroneously) and equipoise is lost [20]. TORS is at this juncture in Canada, with early adopters having implemented the technique, with several other centres planning to implement the technology over the next few years. This provides a key opportunity to test the benefits of TORS.

Identification of biomarkers of radiation or surgical failure would be highly useful to guide patients toward therapies with the highest chance of cure while avoiding unnecessary toxicity. A randomized trial is the ideal setting for biomarker discovery as confounding factors are minimized and follow-up is robust. In our study, the primary tumor and blood samples will undergo whole exome sequencing with copy number analysis. Although the study is not powered for biomarker discovery, the next generation analysis may reveal interesting genetic findings comparing HPV positive and negative cancers. Should a phase III trial be warranted, biomarker discovery will be an integral component in order to identify individuals who would benefit the most from either modality or are at high-risk of treatment related toxicity such as ototoxicity. Reliable biomarkers would represent a tremendous step towards customizing care for the increasing number of patients suffering with OPSCC.
